### Study Integrity

Ethical approval for this study has been obtained from the Human Research Ethics Committees of Royal Brisbane and Women's Hospital and the University of Queensland. The study design will be guided by the CONSORT statement [36]. Each site will be randomly allocated to the Training phase which will be immediately followed by Intervention phase, by the study statistician. Every consecutive patient attending the outpatient oncology department at each site will be screened for eligibility and enrolled if eligible and consenting. Careful documentation of outpatient attendance, subsequent enrolments and consent interviews will ensure that no patient is "selected" for inclusion or exclusion from the study. No patients will be randomised, and whether or not they receive the Intervention will be based on the algorithm depicted in Table 2. It is not possible to blind patients to the Intervention. No health professionals will be randomised. All participating health professionals will receive the training and deliver the psychosocial Intervention to eligible patients. It is not possible to blind health professionals delivering the psychosocial Intervention to the treatment status of patients.

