#### Patients

Inclusion criteria are: (1) aged 18 years or over (2) consecutive patients attending outpatient oncology clinics at each site (3) currently receiving active treatment for cancer OR have completed active treatment within the previous 2 months OR have been diagnosed with recurrent/advanced cancer within the previous 2 months. Exclusion criteria are: (1) inability to speak and read English, (2) receiving current specialised psychological treatment from a psychologist, psychiatrist, or other trained counsellor, (3) currently taking antidepressant medication, (4) health status precludes ability to complete questionnaires and participate in up to four psychosocial Intervention sessions and follow-up at 10 weeks, and (5) recruited in any previous Epoch of this study (that is, patients can only participate during one Epoch).

We will recruit 20 patients per site per Epoch (with the exception of the Training Epochs during which no patients will be recruited) with a total sample size of 600 patients. No patient who has been recruited in a previous Epoch will be eligible to participate in subsequent Epochs. Primary outcome measure is change in HADS score over ten weeks from enrolment to follow-up. Estimates of HADS in similar populations [35] are a mean of 17.8 with SD = 9.0, with a 10%-15% difference in mean change-scores assumed to be clinically significant. To detect this difference, with power = 80%, in a before-after design assuming a correlation 0.5 within patient over time, about 200 patients in each group are needed (Stata IC, version 10). Patients will be clustered by clinic, but we have no data on which to estimate intraclass correlation for the HADS scores; so will assume a design effect of deff = 1.5 to accommodate clustering, and hence we will require 600 patients in all; across five clinics, so we will seek to enrol 120 patients per site.

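### Records of attendance and consent can reveal selective enrolment after a site's step but cannot prevent it, and no rule says which 20 patients fill a site's Epoch if more qualify

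*Protocol article*

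**What the plan says.** All references are to the protocol article, Methods/Design.

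- **Randomisation (Study Integrity).** Sites are allocated, patients are not: "Each site will be randomly allocated to the Training phase which will be immediately followed by Intervention phase, by the study statistician"; "No patients will be randomised, and whether or not they receive the Intervention will be based on the algorithm depicted in Table 2".
- **Blinding (Study Integrity).** "It is not possible to blind patients to the Intervention". The same is said of the health professionals who deliver it. Nothing is said about who screens or takes consent, or what they know.
- **Enrolment rule (Study Integrity).** "Every consecutive patient attending the outpatient oncology department at each site will be screened for eligibility and enrolled if eligible and consenting".
- **Safeguard (Study Integrity).** Keeping records of attendance, enrolments and consent interviews, the article says, "will ensure that no patient is 'selected' for inclusion or exclusion from the study".
- **Intake (Participants, Patients).** "We will recruit 20 patients per site per Epoch", Training Epochs excepted, for a total of 600. A patient may take part in one Epoch only.
- **Exclusion 4 (Participants, Patients).** A patient is excluded if health status rules out, among other things, the ability to "participate in up to four psychosocial Intervention sessions".
- **Analysis (Quantitative analysis).** Change in HADS is compared between patients who enrol in Intervention Epochs and those who enrol in Control Epochs, with a model meant to account for site, time and patient case-mix.

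**The concern.** In a stepped-wedge trial with a fresh group of patients in each period, randomising the order of the sites protects against differences between sites. It does not protect against a change in the kind of patient who enters at a site once its condition changes. Here every patient enters after the site's step has been fixed, and every Intervention Epoch follows a 10-week Training Epoch that involves that site's own clinical staff.

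Two decisions can then vary with condition. A patient may be more or less willing to consent when support is on offer. The judgement of fitness for up to four sessions may be made differently when the sessions will actually take place. Baseline HADS is exposed too: it is one of the two measurements in the primary outcome and it feeds the Table 2 algorithm, and nothing in the article places it before disclosure of the site's condition.

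A log shows such differences afterwards but does not stop them. What is at stake is the validity of the primary comparison, which rests on an unblinded self-report measure. The loosely defined filling of 20 places per cell adds a further opening.

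**Working it through.** **1. The plan's own figures.** Table 1 has 1+2+3+4+5 = 15 Control cells and 5+4+3+2+1 = 15 Intervention cells. 30 × 20 = 600, which is 300 per condition, and 6 × 20 = 120 per site. The other route, 200 × 2 × 1.5 = 600, agrees. The planned difference is 10% to 15% of 17.8, which is 1.78 to 2.67 points. The SD of change is 9.0 × √(2 × (1 − 0.5)) = 9.0. With two-sided alpha 0.05 (assumed; not stated) and 80% power, n per group is 402 at 10% and 179 at 15%. About 200 corresponds to 2.52 points (14.2%). The sample size is not in dispute.

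**2. Why site and epoch terms do not help.** Let X = 1 in Intervention cells and 0 in Control cells. If patients enrolled after the step differ so that their mean change is shifted by b, the expected change in a cell is

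site + epoch + θX + bX = site + epoch + (θ + b)X.

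The model estimates θ + b. Only covariates that carry the difference between the patients can separate b from θ.

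**3. Size of b if selection acts on baseline HADS alone.** With correlation r and equal SDs, expected change given baseline is −(1 − r) × (baseline − mean). A baseline shift of d points therefore gives b = −(1 − 0.5)d = −0.5d if change scores are not adjusted for baseline. The documents give no value for d, so a range is assumed. The false-positive rate uses SE = 9 × √((2/300) × 1.5) = 0.90 and Φ(−1.96 + |b|/SE) + Φ(−1.96 − |b|/SE). This is the plan's two-group approximation, not the standard error of the stepped-wedge model.

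| Assumed shift d (points; SD units) | Spurious change, absolute b | Share of 1.78 | Share of 2.67 | False-positive rate (nominal 5%) |
|---|---|---|---|---|
| 0.9; 0.1 | 0.45 | 25% | 17% | 8% |
| 1.8; 0.2 | 0.90 | 51% | 34% | 17% |
| 2.7; 0.3 | 1.35 | 76% | 51% | 32% |
| 3.6; 0.4 | 1.80 | 101% | 67% | 52% |

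If more distressed patients enrol when help is offered, regression to the mean favours the Intervention. If less distressed patients do, it works against it. Adjustment for baseline HADS removes this component. It does not remove selection on unmeasured traits such as willingness to engage, for which no figure can be given.

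**4. The two enrolment statements.** Twenty places in a 10-week Epoch is 20/10 = 2 per week. Clinic throughput is not given, so a range is assumed. The last column assumes that eligible patients keep consenting throughout the Epoch.

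| Eligible consenters per week | Per Epoch | Weeks to reach 20 | Share not enrolled |
|---|---|---|---|
| 1 | 10 | not reached | 0% |
| 2 | 20 | 10 | 0% |
| 3 | 30 | 6.7 | 33% |
| 4 | 40 | 5.0 | 50% |
| 6 | 60 | 3.3 | 67% |
| 10 | 100 | 2.0 | 80% |

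At up to 2 per week every eligible consenter can be enrolled. Above that, some cannot be, and the article gives no rule for which 20 are taken.

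**The case against.** Several stronger readings are tempting, and the article does not support them.

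- **That the two enrolment statements are incompatible.** This is not shown. They conflict only above 20 eligible consenters per Epoch. Consecutive attendance is also an inclusion criterion, so enrolling consecutively until 20 is a natural joint reading. What stands is that the rule is not stated.
- **That recruiters are known to be unmasked.** This is an inference from the visible Training phase and the unblinded delivery. The text does not say so, and consent procedures may be set out in a fuller protocol that is not shown. What stands is that the article offers documentation as the guarantee, and documentation cannot be one.
- **That exclusion 4 is itself a defect.** It is worded identically for all Epochs, and holding Control patients to the same fitness requirement helps comparability. Only uneven application would cause harm.
- **That patients know their own package before baseline.** Table 2 needs the DT, the risk factors and HADS first. A patient could at most know which condition the site is in.
- **That the analysis ignores patient differences.** The Quantitative analysis section plans case-mix adjustment. That its covariates are unnamed is ordinary SAP detail. If baseline HADS is among them, the bias in the first table above is removed.
- **That a bias of known size is present.** The shifts are assumed and the direction is not determined.

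It is also fair to say that the records already promised are the right raw material for a check.

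**Conclusion.** The concern holds in a limited form. The article promises freedom from selection on the strength of record-keeping. With enrolment after the site's step, no blinding of patients or delivering staff and no described masking of recruiters, records can detect differential consent or eligibility judgements but cannot prevent them. Any resulting difference between the patients enrolled before and after the step enters the Intervention estimate. Site and epoch terms do not take it out, and case-mix adjustment takes out only what is measured.

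The illustrated size, 0.45 to 1.8 points of spurious change, assumes a baseline shift of 0.9 to 3.6 points, correlation 0.5, equal SDs and no baseline adjustment. It shows sensitivity and does not predict an error. The residual from unmeasured selection is not quantified. The gap between enrolling all eligible consenters and taking 20 per cell matters only if throughput exceeds 2 per week, which the article does not report. The change should be made: it is cheap and reduces a possible bias in the primary comparison.

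**What to change.** 1. **Same steps, same order, every Epoch.** Complete the eligibility judgement (including exclusion 4), consent and all baseline questionnaires before the patient is told the site's condition. Use one common information sheet for all sites and Epochs.
2. **One intake rule.** In Control and Intervention Epochs alike, enrol the first 20 consecutive eligible consenting patients from a fixed start date in each Epoch. This reconciles the Patients and Study Integrity sections.
3. **Replace the guarantee with a check.** Say that the records will allow selection to be assessed. Report screened, eligible, consenting and enrolled numbers, and baseline HADS, DT and risk factors, by site and Epoch. Compare Control with Intervention using the primary model's site and epoch terms.
4. **Include baseline HADS in the case-mix adjustment.**

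Cost: patients learn the site's condition somewhat later, and the information sheet probably needs a minor ethics amendment, since approval is already in place. The tables draw on logs and questionnaires already planned. The sample size stays at 600.

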### Measures

#### Health Professional assessment instruments

Demographic details, including professional background and training will be obtained at intake. The following measures will be completed at baseline and on completion of the study when the health professional has completed delivery of the psychosocial Intervention.

##### Psychological distress

The General Health Questionnaire 28 (GHQ) [37] will be used to assess general distress. This is a brief self-report measure which has been extensively used to screen for psychosocial morbidity, with good reliability and validity.

##### Stress and burnout

Occupational stress and burnout will be assessed with the Maslach Burnout Inventory (MBI) [38], a widely-used measure of occupational stress and burnout which assesses Emotional Exhaustion, Depersonalisation and Personal Accomplishment

##### Perceptions of participants

Semi-structured interviews will be conducted with a subset of five health professionals from each site to examine their perceptions of the Training and delivery of the Intervention, including practical aspects of delivery and impediments to the Intervention, as well as reflections about their experience of Clinical Case Review and perceived impact of participation in the study on their clinical practice.

#### Patient assessment instruments

Demographic details, disease stage and current treatment status will be obtained at intake. The following measures will be completed at baseline and 10-week follow-up.

##### Distress

The Distress Thermometer will be used to assess distress. The Distress Thermometer is a self-rated instrument in which patients indicate their Distress (0 = No distress; 10 = Extreme distress), nominating the source of Distress: Practical; Physical; Family; and Emotional or Spiritual/Religious [14]. A cut-off score of 4 has the greatest sensitivity and specificity compared with other validated measures [39].

##### Psychosocial Risk Factors

The Psychosocial Checklist is a structured template based on evidence in the Clinical Practice Guidelines for the Psychosocial Care of Adults with Cancer about known risk factors for development of depression and anxiety in cancer patients [15]. It has been successfully implemented in multiple clinical services across Australia.

##### Mood

The Hospital Anxiety and Depression Scale (HADS) [30] will be used to assess mood. This 14-item scale has good reliability and validity and has been extensively used in studies of cancer patients, cut-off scores of 22 and above representing severe disorder, and less than 8 representing no disorder.

##### Unmet Psychological Supportive Care Needs

The Supportive Care Needs Survey-Short-Form SCNS-SF 34 [40] will assess patients' needs for help over the last month across the following domains: Psychological; Health Systems and Information; Patient Care and Support, and Physical and Daily Living needs.

##### Quality of life

FACT-G (Functional Assessment of Cancer Scale - General) [41] is a widely-used measure of quality of life in the cancer population, with well-being subscales: Physical; Social/family; Emotional, and Functional.

EQ-5 D (EuroQoL) [42] is a brief self-report measure of quality of life from which a QALY can be calculated. This measure has been used in intervention studies with depressed patients [43].

##### Experience of demoralisation

DS (Demoralisation Scale) is a 24 item self-report scale with a Cronbach alpha of .96, measuring depression commonly seen in the physically ill [44]. Norms have been established in a non-clinical sample [45].

##### Health service use

Patients will maintain a record of visits to General Practitioners and any contact with community or hospital-based support services, using a structured template.

### Statistical analyes

#### Quantitative analysis

We will compute and compare the average change in HADS scores among patients enrolling during Intervention Epochs with scores of patients enrolling during Control Epochs. The strength of the stepped-wedge design is that we will be able to account for systematic differences between sites and times during the trial, and also for case-mix differences between patients.

We will use a patient-level hierarchical analysis model to accommodate these potentially confounding factors. With this model, we can adjust for case-mix differences between sites, as well as allow for specific site characteristics (other than presence/absence of the Intervention). A generalised estimating equation (GEE) linear or logistic model will be implemented [28] to estimate the effect of the Intervention on the patients' change in HADS scores and the prevalence of depression "caseness" at each site. Stata Version 10 (StataCorp, 2008) will be used for all statistical analyses.

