## Methods/Design

### Study aims and hypotheses

The study's primary aim is to evaluate the effectiveness of a brief psychosocial Intervention in reducing depression and anxiety in patients with cancer who are distressed, but not severely depressed, or who are at risk of becoming depressed. The Intervention will be delivered by health professionals who have participated in focused training and who receive clinical supervision during delivery of the Intervention. Additional aims are to examine the impact of the psychosocial Intervention on patient unmet needs, quality of life, and scores of demoralisation.

Secondary aims are to examine any impact on stress and burnout and psychological adjustment of the health professionals who deliver the psychosocial Intervention, to assess the feasibility of integration of the Intervention into clinical practice, and to identify health professional, systems and patient barriers to the implementation of this model of systematic tailored psychosocial Interventions in clinical care.

It is hypothesised that:

1. Patients receiving the Intervention will demonstrate greater improvement in depression/anxiety scores and reduction in depression/anxiety "caseness" compared with patients receiving Usual Care.

2. The Intervention will be associated with lower rates of depression/anxiety and increasing reduction in depression/anxiety scores over time in patients of the cancer services.

3. There will be no changes in health professional stress and burnout.

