#### iii) High-intensity Intervention

Patients who have high levels of distress as measured on the HADS (scores of 22 or greater) have needs beyond the training of the health professionals participating in this study and require a high-intensity Intervention. All patients in this category will be referred for Specialised Treatment (high-intensity Intervention) with an appropriately qualified practitioner via a pre-defined clinical pathway at the respective site.

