#### iv) Usual Care

Patients with *no *current distress (DT Score < 4) and *no *risk factors (on Psychosocial Checklist) will not receive any additional information or psychosocial support related to coping with cancer beyond the normal clinical practice at the site where they are receiving cancer care. They will continue to participate in follow-up or cancer-specific treatment as usual. They will not have contact with the trained health professionals at that site other than in the usual course of clinical care.

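### The only stated comparison takes all enrolled patients by epoch; it fits Hypothesis 2 but does not estimate the effect in the population of the primary aim and Hypothesis 1

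*Protocol article*

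**What the plan says.** **Aim.** Under Study aims and hypotheses, the primary aim concerns "patients with cancer who are distressed, but not severely depressed, or who are at risk of becoming depressed". Hypothesis 1 begins "Patients receiving the Intervention will demonstrate greater improvement in depression/anxiety scores" and sets these patients against patients on Usual Care. Hypothesis 2 is different in kind: it expects "increasing reduction in depression/anxiety scores over time in patients of the cancer services".

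**Enrolment.** The Patients section admits "consecutive patients attending outpatient oncology clinics at each site", subject to age, treatment status, language, current psychological treatment, antidepressant use and health status. It has no criterion on the DT, the HADS or the Psychosocial Checklist. Study Integrity confirms this: "Every consecutive patient attending the outpatient oncology department at each site will be screened for eligibility and enrolled if eligible and consenting". It then says that Table 2 decides which of the enrolled patients receive the Intervention.

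**Enrolled patients outside the Intervention.** Patients with DT below 4 and no risk factors "will not receive any additional information or psychosocial support related to coping with cancer beyond the normal clinical practice". Patients with HADS 22 or more "have needs beyond the training of the health professionals participating in this study" and are referred to specialised treatment.

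**Comparison.** The Patients section makes change in HADS over ten weeks the primary outcome. The only comparison given for it, under Quantitative analysis, is to "compare the average change in HADS scores among patients enrolling during Intervention Epochs with scores of patients enrolling during Control Epochs". The sample size of 600 also counts every recruited patient.

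**The concern.** The stated aim and the stated comparison refer to different populations. The aim leaves out patients who are neither distressed nor at risk, and those who are severely depressed. The comparison takes in both. Planned case-mix adjustment does not cure this, because adjusting for a covariate does not change who is being averaged over.

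The two extra groups act differently.

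- **Usual-care group.** It is offered nothing extra in either epoch type, so it pulls the pooled difference towards zero.
- **HADS 22 or more.** The article does not say whether the specialist pathway also operates in Control Epochs. If it does, this group dilutes too. If referral starts only in Intervention Epochs, the pooled difference takes in effects of specialist treatment, of unknown direction, in patients whom the aim excludes.

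In either case the estimate is not the effect of the brief Intervention in the patients for whom it was designed. A null or positive result could be misread as an answer to the primary question.

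**Working it through.** **1. Reproduce the plan's figure.** Inputs from the Patients section: HADS mean 17.8, SD 9.0, within-patient correlation 0.5, power 80%, difference 10%-15%, design effect 1.5. Alpha is not stated; 0.05 two-sided is assumed.

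- SD of change = 9.0 × √(2 × (1 − 0.5)) = 9.0.
- Difference detectable with 200 per group = 9.0 × (1.96 + 0.84) × √(2/200) = 2.52 points.
- 2.52 / 17.8 = 14.2%, inside the stated 10%-15%.
- 2 × 200 × 1.5 = 600. Table 1 has 15 control cells and 15 intervention cells, and 20 × 15 = 300 per condition.

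The 600 is reproduced, and it counts all recruited patients.

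**2. How large might the extra groups be?** The article gives no shares. A normal approximation to its planning distribution, with continuity correction, gives:

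- HADS 22 or more: 1 − Φ((21.5 − 17.8)/9) = 0.34
- HADS below 8: Φ((7.5 − 17.8)/9) = 0.13
- HADS 8-21: the remainder, 0.53

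Let p be the share in the low- and medium-intensity groups. If everyone below HADS 22 belongs there, p is about 0.66. If all of HADS 8-21 but nobody below 8 belongs there, p is about 0.53. A lower value is possible if patients with DT below 4, no risk factors and HADS 8-21 go to usual care. Since p is unknown, a range is shown.

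**3. Scenario.** Assume a true effect of 2.52 points within the low- and medium-intensity groups and none elsewhere, with SD 9.0 and design effect 1.5 in either set.

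- Pooled effect = p × 2.52; pooled power = Φ(2.80p − 1.96)
- Restricted power, with 600 still enrolled = Φ(2.80√p − 1.96)

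| p | Pooled effect | Pooled power | Restricted power | Enrolled to analyse 600 (600/p) |
|---|---|---|---|---|
| 0.9 | 2.27 | 71% | 76% | 667 |
| 0.8 | 2.02 | 61% | 71% | 750 |
| 0.7 | 1.76 | 50% | 65% | 858 |
| 0.66 | 1.66 | 46% | 62% | 910 |
| 0.5 | 1.26 | 29% | 51% | 1200 |

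Because √p exceeds p for every p below 1, restriction gives more power than pooling whenever the other groups show no effect. It does not bring power back to 80%.

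**4. Can the restricted set be formed?** The DT, Psychosocial Checklist and HADS are all listed as baseline measures for patients, so the same rule can be applied in both epoch types. The rule itself is not settled for DT below 4 with HADS 8 or more:

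- The medium-intensity section covers HADS 8-21 whatever the risk factors, and the high-intensity section covers all with HADS 22 or more.
- The Usual Care section and Table 2 send DT below 4 without risk factors to usual care, whatever the HADS score.
- Table 2 has no column for DT below 4 with risk factors and HADS 8 or more.

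**The case against.** **An analysis plan not shown may define the set.** Articles often leave analysis sets to it, and such a plan could restrict the comparison. But this article is not merely silent. It states a contrast by enrolment epoch and a sample size, and both count all enrolled patients. Followed as written, they miss the primary aim.

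**All enrolled is the natural stepped-wedge contrast, and the Discussion describes a whole model of screening and tiered care.** This stands for Hypothesis 2, where the comparison should be kept. It does not make that contrast an estimate for the narrower population in the primary aim.

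**The power loss depends on where the planned difference is placed.** This also stands. The Patients section states a difference in mean change scores and does not tie it to a subgroup. If it was meant as the difference between all enrolled patients, the sample size and the comparison agree and the calculated loss does not arise. A reader might infer that the trial is shown to be underpowered; the article does not support that.

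**Other readings that go too far.** A reader might take Hypothesis 1 together with the Usual Care section as a plan to compare treated, distressed patients with undistressed ones, a contrast driven by regression to the mean. The Quantitative analysis section compares by epoch, so no such analysis is planned; the wording of Hypothesis 1 is loose. A reader might also take the 35% distress prevalence in the Background as p. It is a different quantity: it can include patients at HADS 22 or more, and it omits at-risk patients without distress.

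**Conclusion.** The point holds. The one stated comparison for the primary outcome covers all patients enrolled by epoch. It matches Hypothesis 2, and leaves the primary aim and Hypothesis 1 without a matching analysis. This follows from the text and needs no numerical assumption.

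The size of the consequence is conditional. Dilution is the expected effect of the usual-care group. For HADS 22 or more, dilution towards zero cannot be asserted, because the article does not say whether referral operates in Control Epochs. The power figures (46% pooled against 62% restricted at p = 0.66; 29% against 51% at p = 0.5) are scenarios. They rest on an unstated p, two-sided alpha 0.05, a 2.52-point effect confined to the low- and medium-intensity groups, and an unchanged SD and design effect.

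**What to change.** 1. Reconcile the medium-intensity, high-intensity and Usual Care sections with Table 2 for patients with DT below 4 and HADS 8 or more. The analysis set cannot be defined until this is done.
2. Under Quantitative analysis, define the primary analysis set for the primary aim and Hypothesis 1 as patients, in Control and Intervention Epochs alike, whose baseline DT, Psychosocial Checklist and HADS place them in the low- or medium-intensity groups. Analyse them by the epoch condition at enrolment, whatever they actually received.
3. Keep the comparison of all enrolled patients as the analysis for Hypothesis 2.
4. In Hypothesis 1, replace 'receiving Usual Care' with 'enrolled in Control Epochs'.
5. State to which population the 10%-15% difference applies, and restate the power for the restricted set at 600 enrolled.

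**Cost.** No new data are needed, since all three classifiers are collected at baseline. But this is more than a wording change. The allocation rules must be settled first, the primary set is smaller, and in the scenario above its power at 600 enrolled is below 80%. Analysing 600 patients in that set would take about 910 enrolled at p = 0.66, or 1200 at p = 0.5.
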